**Figure 3 F3:**
[figure not shown]
(A) Power curve for the first primary outcome, proportion of kidneys that are transplanted on first offer. The curves show the increase in power as the cluster size increases, for 20 clusters, 5 steps, 4 clusters crossing over at each step and the proportion under control and intervention of 28% and 39%, respectively. The black curve shows the power for the base values of within-period intracluster correlation (WP-ICC) and cluster autocorrelation (CAC) (0.03 and 0.92, respectively), and the remaining curves show for lower and upper levels of the WP-ICC (0 and 0.08, respectively) and CAC (0.74 and 1, respectively). (B) Power curve for the second primary outcome estimated glomerular filtration rate measured at 12 months after transplant. The curves show the increase in power as the cluster size increases, for 20 clusters, 5 steps, 4 clusters crossing over at each step and the mean difference of 6 and SD of 16.06. The black curve shows the power for the base values of WP-ICC and CAC (0.06 and 0.08, respectively), and the remaining curves show for lower and upper levels of the WP-ICC (0.01 and 0.11, respectively) and CAC (0.06 and 0.10, respectively).

#### Second primary outcome: eGFR measured at 12 months after transplant

Data were extracted on all recipients who received a kidney only transplant from deceased donors (DBD and DCD) aged ≥60 years, in the UK (excluding transplants at Cambridge) between 1 April 2014 and 31 March 2016. The median number of transplant recipients per cluster per month was 2, hence providing an average cluster-period size of 8. eGFR was calculated using the 4-variable Modification of Diet in Renal Disease (MDRD) formula using uncalibrated serum creatinine measurements,^20^ hence if missing data were present for the recipients sex, age, ethnicity and serum creatinine at 12 months, then eGFR could not be calculated (19%). The mean eGFR was 41.91 with an SD of 16.06.

A mixed linear regression model was fitted to this data, with a continuous outcome (eGFR), a fixed effect for date of transplant (which was converted into year quarter, ie, six, 4-month time periods), a random effect for cluster and a random interaction between cluster and period. From this model, the WP-ICC and CAC were calculated as 0.06 and 0.08, respectively. Assuming an average cluster-period size of 8 (=2×4 clusters), this outcome will have 89% power to detect a mean difference in eGFR of 6 mL/min (assuming a significance level of 2.5%). We checked the sensitivity of this calculation by looking at an increase, and separately a decrease, of 0.5 in the mean difference; and by varying the WP-ICC by ±0.05 and CAC by ±0.016 (which equates to ±20% of the base CAC). The trial has within the region of 80% power for all anticipated values of WP-ICC and CAC, and likely values of cluster-period sizes. The power curve, with the mean difference set as 6, is shown in figure 3B. As the CAC was particularly small, we separately explored the effects of a large CAC value (0.8) and found this had minimal impact.

### Analysis plan

The primary outcome analyses will be performed according to the intention to treat. This will include all eligible patients for whom data have been obtained and will be analysed with respect to the treatment specified by the allocated randomisation order. The primary outcomes will be compared using two-sided tests and at a 2.5% significance level. Departures from randomisation at cluster level are defined as any cluster which does not switch to the intervention when stated in the randomisation order. A cluster is able to withdraw at any point during the trial. Per protocol analysis, which will exclude departures from randomisations and any cluster withdrawals, will also be completed for both primary outcomes of the trial. In situations where a pair of kidneys are transplanted as a ‘dual’ transplant into one recipient (eg, when the biopsy score is >4), this will be counted as half a transplant (in terms of utilisation, not as effective as performing two single transplants, but better than discard).

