**Methods and analysis:**

PITHIA is an open, multicentre, stepped-wedge cluster randomised study, involving all UK adult kidney transplant centres. At 4-monthly intervals, a group of 4–5 randomly selected clusters (transplant centres) will be given access to remote, urgent, digital histopathology (total intervention period, 24 months). The trial has two primary end points: it is powered for an 11% increase in the proportion of primary kidney offers from deceased donors aged over 60 years that are transplanted, and a 6 mL/min increase in the estimated glomerular filtration rate of recipients at 12 months post-transplant. This would equate to an additional 120 kidney transplants performed in the UK annually. Trial outcome data will be collected centrally via the UK Transplant Registry held by NHS Blood and Transplant (NHSBT) and will be analysed using mixed effects models allowing for clustering within centres and adjusting for secular trends. An accompanying economic evaluation will estimate the cost-effectiveness of the service to the National Health Service.

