****Trial registration** number:**

ISRCTN11708741; Pre-results.

Strengths and limitations of this studyProspective, randomised evaluation of a clinical service using a novel stepped-wedge cluster design which avoids contamination of trial groups, while remaining acceptable to patients and study centres.The first national, 24 hours streamlined digital histopathology service, which will support all adult kidney transplant centres in the UK and is likely to have applications beyond the trial setting.Example of a low cost ‘registry-based trial’ which uses routinely collected data and has a concomitant economic evaluation to determine cost-effectiveness.Use of two primary end points (and therefore nine possible trial outcomes) increases the possibility of an equivocal, rather than definitive result.To conserve power, the study will not be stopped early except on the grounds of patient safety.Thus, there is a risk that access to histopathology may lead to fewer kidney transplants being performed.

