### Study hypotheses

This trial will test the hypothesis: ‘Provision of a national 24/7 preimplantation biopsy service results, at reasonable cost, in transplantation of a greater proportion of kidneys offered from deceased donors aged ≥60 years, and/or improves kidney transplant function at 1-year post-transplant. Numbers of deceased donor kidney transplants performed annually in the UK are consequently significantly increased or improved in quality’.

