#### First primary outcome: proportion of kidneys that are transplanted on first offer

Data were extracted on first kidney offers from potential deceased (DBD and DCD) donors aged 60 years and over, in the UK between 1 April 2014 and 31 March 2016. Offers of simultaneous pancreas kidney, multiorgan, fast-track and any offers to Cambridge were excluded. The percentage of first offers which were transplanted was 28.4%. The median number of first offers per cluster per month was 4.38. A mixed linear regression model was fitted to the extracted data, with a binary outcome (whether the offer resulted in a transplant), a fixed effect for date of offer (which was converted into year quarter, ie, six, 4-month time periods called period henceforth), a random effect for cluster and a random interaction between cluster and period. From this model, the within-period intracluster correlation (WP-ICC) and cluster autocorrelation (CAC) were calculated as 0.03 and 0.92, respectively. Assuming an average cluster-period size of 18, to detect a 11% increase in the number of first offers transplanted, the trial will have 85% power (assuming a significance level of 2.5%) and would represent an increase from 28% to 39% acceptance, which we believe would be considered clinically important. We have not allowed for attrition in this calculation as there is unlikely to be any missing data, due to the robustness of the offering data collected by NHSBT. We checked the sensitivity of this calculation by looking at an increase, and separately a decrease, of 2% in the baseline proportion, by varying the WP-ICC (lower WP-ICC set as 0 and upper WP-ICC set as 0.08) and the CAC (lower CAC set as 0.74 and upper CAC set as 1. The trial has within the region of 80% power for all anticipated values of WP-ICC and CAC, and likely values of cluster-period sizes. The power curve, with the baseline proportion set as 28%, is shown in figure 3A.

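### The fixed 2.5% test for each primary outcome is valid, but Holm's step-down would keep the same 5% family-wise error and raise the chance that both succeed from about 76% to about 84% if both design effects are true

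*Protocol article*

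**What the plan says.** The abstract of the protocol article says "The trial has two primary end points": the proportion of first offers transplanted, and eGFR at 12 months. The Analysis plan section fixes the test for each: "The primary outcomes will be compared using two-sided tests and at a 2.5% significance level". Both sample size sections use the same 2.5% level, giving 85% power for the first outcome and 89% for eGFR. No step-down rule or passing on of alpha is described, and no family-wise level is stated.

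The hypothesis in Study hypotheses is disjunctive. The service is to increase the proportion of kidneys transplanted "and/or improves kidney transplant function at 1-year post-transplant". The strengths and limitations list concedes a weakness: "Use of two primary end points (and therefore nine possible trial outcomes) increases the possibility of an equivocal, rather than definitive result".

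Analysis of primary and secondary outcomes plans a 95% confidence interval for the eGFR difference. Full statistical detail is left to a statistical analysis plan, but the level of the primary tests is fixed in the article itself.

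**The concern.** With two primary outcomes and an and/or hypothesis, 2.5% for each is most naturally read as a Bonferroni split of 5%. For two unordered hypotheses, Holm's procedure dominates that split. It has the same family-wise bound under any correlation, needs no extra data, and can only add rejections.

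What is at stake is the second outcome. Under the fixed rule, a trial that wins on one outcome and has p between 0.025 and 0.05 on the other must report the latter as non-significant, although the 5% family-wise budget would allow it to be claimed. A split verdict of this kind is one form of the equivocal result that the authors list as a limitation.

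**Working it through.** **Inputs from the protocol article.**
- Level: two-sided 2.5% per outcome (Analysis plan).
- First outcome: 28% to 39%, WP-ICC 0.03, CAC 0.92, cluster-period size 18, stated power 85%.
- eGFR: difference 6 mL/min, SD 16.06, WP-ICC 0.06, CAC 0.08, cluster-period size 8, stated power 89%.
- Layout: 20 clusters, 5 steps, 4 clusters per step (legend to figure 3), hence 6 periods.

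**Step 1: reproduce the stated powers.** I used generalised least squares on cluster-period means, with fixed period effects and random cluster and cluster-by-period effects. Power = Φ(effect/SE − 2.2414), where 2.2414 is the two-sided 2.5% critical value.
- First outcome (variance averaged over 28% and 39%): SE 0.0335, 0.11/0.0335 = 3.284, power Φ(1.043) = 85.1%. Stated: 85%.
- eGFR: SE 1.7205, 6/1.7205 = 3.487, power Φ(1.246) = 89.4%. Stated: 89%.

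Both reproduce. The rest uses the stated, rounded powers.

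**Step 2: power at 5%.** The noncentralities are 2.2414 + 1.0364 = 3.2778 and 2.2414 + 1.2265 = 3.4679. With the 5% critical value of 1.9600:
- First outcome: Φ(3.2778 − 1.9600) = 90.62%.
- eGFR: Φ(3.4679 − 1.9600) = 93.42%.

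**Step 3: both significant, independent test statistics, both design effects true.**
- Fixed 2.5%: 0.85 × 0.89 = 75.65%.
- Holm (one p ≤ 0.025, the other ≤ 0.05): 0.85 × 0.9342 + 0.9062 × 0.89 − 0.7565 = 84.41%.
- Power for each outcome under Holm: 0.85 + 0.0562 × 0.89 = 90.0%, and 0.89 + 0.0442 × 0.85 = 92.8%.

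**Step 4: what does not change.** At least one significant: 0.85 + 0.89 − 0.7565 = 98.35% under either rule, because both open with the same 2.5% threshold. Exactly one significant falls from 98.35 − 75.65 = 22.7% to 98.35 − 84.41 = 13.9%.

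**Step 5: correlation between the test statistics.** The article gives none, so a range is assumed.

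| Correlation | Fixed 2.5%, both | Holm, both | Gain (points) |
|---|---|---|---|
| −0.5 | 74.2% | 84.0% | 9.8 |
| 0 | 75.65% | 84.41% | 8.8 |
| 0.8 | 81.5% | 87.4% | 5.9 |

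**Step 6: only one effect real (independence).**
- First outcome real, eGFR null: power for the first outcome is 0.85 + 0.0562 × 0.025 = 85.1%, against 85.0%. The chance of a false eGFR claim is 0.025 + 0.025 × 0.85 = 4.6%, against 2.5%.
- eGFR real, first outcome null: power for eGFR is 0.89 + 0.0442 × 0.025 = 89.1%, against 89.0%. The chance of a false claim on the first outcome is 0.025 + 0.025 × 0.89 = 4.7%, against 2.5%.

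**Step 7: family-wise error.** If both nulls are true, Holm makes a false claim only when the smaller p is at most 0.025, which has probability at most 2 × 2.5% = 5% (1 − 0.975² = 4.94% under independence). If one null is true, it is rejected only when its p is at most 0.05, again at most 5%. Neither argument uses the correlation. A simulation of 2 million draws gave 4.95% with both nulls true and independent, and 5.0% with one null true and the other effect very large.

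**The case against.** The strongest reply is that nothing here is wrong. A fixed 2.5% per outcome is valid and simple, and the article applies it consistently in the power calculations and the test rule. That stands. A reader might infer that the plan contains an error or that the trial is underpowered. The article does not support either: its powers reproduce, and under its and/or hypothesis one positive outcome is enough, with a 98.35% chance of at least one under either rule if both design effects are true.

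The benefit is also conditional. The Discussion describes success as more transplants with graft quality maintained, which is an effect on the first outcome and none on eGFR. Holm then adds almost nothing (85.0% to 85.1%). The article never says that both design effects are expected together. This stands too and limits the size of the point.

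A reader might also infer that Holm costs nothing in error. That is too strong. The family-wise bound is unchanged, but the chance of a false claim on one outcome can nearly double when the other effect is real (2.5% to 4.6% for eGFR). Holding each outcome at 2.5% whatever the other shows is a defensible choice. The 5% family-wise aim is itself inferred.

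Finally, nine possible outcomes most naturally means better, unchanged or worse on each of two endpoints, so equivocal includes opposite directions. Holm does not resolve those. The fall in split verdicts is shown only for two favourable effects.

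**Conclusion.** The point holds as a cheap improvement of low severity (nice to have). The fixed 2.5% rule is valid. If its purpose is a 5% family-wise error, Holm's step-down gives the same strong control and is never less powerful.

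If both design effects are true and the stated powers hold, the chance of winning on both outcomes goes from about 76% to about 84% under independence, a gain of about 10 to 6 points over correlations from −0.5 to 0.8. There is no gain in the chance of at least one success, and almost none if only one effect is real. The conclusion rests on the inferred 5% family-wise level and on the disjunctive hypothesis.

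**What to change.** In Analysis plan, replace the fixed level with a rule such as: the smaller of the two primary p values is tested at two-sided 2.5%; if it is significant, the other is tested at two-sided 5% (Holm), which holds the family-wise error at 5%. Make the change before any outcome data are seen, and carry it into the statistical analysis plan.

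Leave both sample size calculations at 2.5%. That is the conservative case and needs no more centres, kidneys or follow-up.

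In Analysis of primary and secondary outcomes, report 97.5% confidence intervals for both primary outcomes in place of the 95% interval now planned for eGFR. Add a note that an outcome won at the second step may have a 97.5% interval that includes the null. The intervals need attention even if the fixed rule is kept: a 95% interval beside a 2.5% test can exclude zero for a result declared non-significant.

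The cost is one sentence and one footnote, plus accepting a per-outcome error of up to 5% rather than 2.5% when the other outcome is significant. If the trial team prefers to hold each outcome at 2.5% regardless, a sentence saying so would also settle the matter.

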#### Analysis of primary and secondary outcomes

All primary and secondary outcomes will adjust for calendar time, since the intervention is sequentially rolled out, and cluster, as participants within the same centre are not independent.

The primary aim of the study is to evaluate whether there is a difference in the use of kidneys from older donors before and after exposure to the intervention. For the first primary outcome, a logistic regression model, with random effects for cluster and cluster by period; and adjusting for period (fixed effect), will be used for the hypothesis test and to obtain the associated CI. This will be supplemented with a risk difference obtained from a binomial model with identity link, random effects for centre and centre by period; and adjusting for period (fixed effect). The absolute numbers will be presented by trial arm.

Mean eGFR values in each treatment group at 1 year will be compared using a normal regression model, adjusting for random cluster effect, random cluster by period interaction and a fixed effect for period. As eGFR at 12 months is only recorded for patients who are alive with a functioning graft at 12 months, the primary analysis will be complete case and there will be no imputation for missing values. The number of participants surviving to 12 months will be reported and of those the number who have a 12-month eGFR recorded. The adjusted mean and SD eGFR at 12 months will be reported by treatment arm, alongside the adjusted treatment difference with 95% CI and p value.

A sensitivity analysis will repeat the analysis for the second primary outcome but with the following imputations: if a patient’s graft failed within 12 months, the eGFR at 12 months will be set to the mean value for patients on dialysis in the UK (currently 8.5 mL/min/1.73 m^2^).^24^ If a patient died with a functioning graft within 12 months of transplant, the 12-month eGFR will be set to the mean value at 12 months for all UK transplant patients with a functioning transplant at 1 year (currently 49.4 mL/min/1.73 m^2^). This method assumes that deaths with a functioning graft will occur at random. Multiple imputation was considered futile as insufficient clinical data are collected at the 12-month time point to accurately impute any missing measurements.

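### The first primary model is valid and reaches its stated 85% power, but leaves unused each centre's pre-trial first-offer rate, which could add about 5 to 6 points of power if centre rates stay stable and less if they drift

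*Protocol article*

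**What the plan says.** The section on analysis of primary and secondary outcomes fixes the terms of the first primary model: "a logistic regression model, with random effects for cluster and cluster by period; and adjusting for period (fixed effect), will be used for the hypothesis", meaning the primary test. A supporting identity-link binomial model for the risk difference has the same terms. Neither contains information from before the trial.

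The sample size section for the same outcome shows that such information exists: "Data were extracted on first kidney offers from potential deceased (DBD and DCD) donors aged 60 years and over, in the UK between" two dates that span the 24 months to the end of March 2016. The source was the UK Transplant Registry, with the relevant offer exclusions. The offers were divided into six 4-month periods and modelled with centre and centre-by-period random effects, from which "the within-period intracluster correlation (WP-ICC) and cluster autocorrelation (CAC) were calculated as 0.03 and 0.92, respectively".

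The Randomisation section also uses historic data, but only cluster sizes. The baseline practice mentioned under Control condition is activity observed after the trial has begun.

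**The concern.** A cluster autocorrelation of 0.92 means that, by the plan's own estimate, a centre's underlying acceptance rate barely moves between periods. Its pre-trial rate should then predict its trial-era rate well. The first group to cross over has only one control period, about 18 offers per centre, from which to show its own level; later groups have two to five. Between-centre variance that existing data could explain therefore stays in the primary comparison.

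Power is at stake, not validity. All UK adult kidney transplant centres already take part, so no further clusters can be recruited, and more efficient analysis is one of the few ways left to gain precision.

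**Working it through.** **Inputs**

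- Design for power (Figure 3 legend): "20 clusters, 5 steps, 4 clusters crossing over at each step and the proportion under control and intervention of 28% and 39%, respectively". This gives six periods, the first all control.
- Cluster-period size: "Assuming an average cluster-period size of 18".
- Effect: the difference "would represent an increase from 28% to 39% acceptance", that is 0.11.
- WP-ICC 0.03 and CAC 0.92 (sample size section).
- Test: "The primary outcomes will be compared using two-sided tests and at a 2.5% significance level", so z = 2.241.
- Clusters randomised: 22 (Description of study design). I assume groups of 4, 4, 4, 5 and 5.

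**Step 1: reproduce the stated power.** Generalised least squares on cluster-period means, with fixed period effects and the plan's correlation structure.

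- Binomial variance: s² = (0.28×0.72 + 0.39×0.61)/2 = 0.21975
- Centre variance: 0.03×0.92×s² = 0.0276 s²
- Centre-by-period variance: 0.03×0.08×s² = 0.0024 s²
- Sampling variance of a cluster-period mean: 0.97×s²/18 = 0.0539 s²
- Standard error of the treatment effect: 0.0335
- Power = Φ(0.11/0.0335 − 2.241) = Φ(3.284 − 2.241) = 85.1%

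The plan says that "the trial will have 85% power (assuming a significance level of 2.5"%), so its figure reproduces.

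**Step 2: add the pre-trial rate.** The share of centre variance explained by a centre's mean over six pre-trial periods of 18 offers is

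0.0276 / (0.0276 + (0.0024 + 0.0539)/6) = 0.746,

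which leaves about 25% of the centre variance. The standard error falls to 0.0307 and power becomes Φ(3.587 − 2.241) = 91.1%. Entering the six periods as extra control periods gives the same result. The planned variance is (0.0335/0.0307)² ≈ 1.19 times the variance with pre-trial data.

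**Step 3: vary the assumptions.** The 24-month pre-trial window is used unless stated. The decay rates and the length of the gap are my assumptions.

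| Setting | Without | With | Gain (points) |
|---|---|---|---|
| 20 centres, CAC 0.92 at every lag | 85.1% | 91.1% | 5.9 |
| Same, 12 months of pre-trial data | 85.1% | 89.2% | 4.1 |
| 22 centres, CAC 0.92 at every lag | 88.6% | 93.6% | 5.1 |
| 20 centres, decay 0.92 per period, no gap | 83.5% | 86.0% | 2.5 |
| 20 centres, decay 0.95, no gap | 84.4% | 87.7% | 3.3 |
| 20 centres, decay 0.97, no gap | 85.1% | 89.2% | 4.0 |
| 20 centres, decay 0.92, 2-year gap | 83.5% | 84.3% | 0.7 |
| 20 centres, decay 0.95, 2-year gap | 84.4% | 85.9% | 1.4 |
| 20 centres, decay 0.97, 2-year gap | 85.1% | 87.5% | 2.4 |
| 20 centres, WP-ICC 0.08, CAC 0.92 | 80.7% | 89.8% | 9.0 |
| 20 centres, WP-ICC 0.08, CAC 0.74 | 72.2% | 81.9% | 9.7 |
| 20 centres, WP-ICC 0 | 95.9% | 95.9% | 0 |

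Gains are taken before rounding. With 22 centres and no gap, the three decay rates give gains of 2.2, 2.8 and 3.5 points. For eGFR, the plan's CAC of 0.08 makes the gain negligible (89.4% to 89.6%).

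All figures are on the risk-difference scale of the sample size calculation. The logistic model was not simulated.

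**The case against.** The strongest reply is that nothing here is wrong. The analysis model has the same structure as the model used for sizing, it is unbiased and it achieves the power claimed. Adjustment covariates are often left to an analysis plan, and the article defers full details to one. The first part stands: this is an improvement and not a correction. The second only limits the point, because the article does state the terms of the model that carries the hypothesis test.

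A reader might infer that the plan gives up a flat six points of power. The documents do not support that. The CAC was estimated within one 24-month window, whereas the proposed analysis would span 48 months, and the article itself expects transplant practice to evolve. Six points is also the 20-centre figure; 22 are randomised. The extract used for sizing ends in March 2016 and the article gives no trial start date, so reusing that extract could leave a gap of unknown length.

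A reader might also infer that the planned model knows nothing of a centre's own level. It does: each centre contributes at least one control period, and the random effects use information both between and within centres.

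Finally, a logit-scale covariate does not suit the identity-link model. That objection is right, and the fix allows for it.

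**Conclusion.** The point holds as a gain in efficiency. The gain is 5.9 points with 20 centres and 5.1 with 22, if the correlation of 0.92 applies at every lag back to the pre-trial periods. It is about 2 to 4 points if correlation decays at 0.92 to 0.97 per period and the pre-trial window runs up to trial start. It is about 1 point after a two-year gap with decay of 0.92 to 0.95, and zero if centres do not differ. The size of the WP-ICC drives it most: the largest gains are at the plan's upper value of 0.08.

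The results assume equal cluster-period sizes of 18, both before and during the trial, and a normal reference distribution. It would be wrong to read them as showing bias or a failure to reach 85% at the planning values.

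**What to change.** For the first primary outcome only, add one centre-level covariate: the centre's proportion of first offers transplanted over the 24 months immediately before trial start, with the trial's eligibility rules and offer exclusions. Enter it on the logit scale in the logistic model and on the proportion scale in the identity-link model. Fix it before allocation is revealed, so that it cannot depend on the crossover order. Keep the model without it as a sensitivity analysis.

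The cost is a fresh extract from a registry whose collection is mandatory, one degree of freedom at centre level and a sentence in the analysis plan. If centre practice has drifted, the benefit shrinks towards the lower figures above. The eGFR model needs no change.

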#### Safety outcome measures

Biopsy-related complication rate.

*Subgroup analyses* (the primary outcome will be replicated for each subgroup):DBD donors only;DCD donors only;Donors who are aged >70 years;Centres with historically low median UK Kidney Donor Risk Index of transplanted DCD kidneys (low-risk transplants compared with overall UK activity).

The trial will use data that are routinely collected on the national UK Transplant Registry (UKTR), held by NHSBT. The national registry has a mandatory collection system that produces comprehensive information on organ donors, organs, transplants and recipients.

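### The first primary model has no donor covariate although donor age and DBD/DCD type are known for every offer: a modest missed gain in power and in protection against chance imbalance, not a bias

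*Protocol article*

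**What the plan says.** Under *Analysis of primary and secondary outcomes*, the article sets a general rule: "All primary and secondary outcomes will adjust for calendar time, since the intervention is sequentially rolled out, and cluster". For the first primary outcome it names a logistic model with random effects for cluster and cluster by period, "adjusting for period (fixed effect), will be used for the hypothesis test and to obtain the associated CI". A supplementary binomial model with identity link, carrying the same terms, gives the risk difference. Neither model contains a donor characteristic.

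Elsewhere the article shows that donor age and type are available and matter:

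- *Inclusion and exclusion criteria*: the analysis set is defined by donor age (60 or over) and by DBD or DCD donation, so both must be known for each offer.
- *Safety outcome measures* (data-source paragraph): the mandatory national registry produces "comprehensive information on organ donors, organs, transplants and recipients".
- *Safety outcome measures* and *Other analyses*: DBD donors, DCD donors and donors over 70 are separate subgroups.
- *Patient and public involvement*: discard of kidneys from elderly DCD donors is described as particularly high.

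*Other analyses* leaves full statistical detail to a statistical analysis plan, which is not shown.

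**The concern.** Each centre is compared with itself over time, in cells averaging 18 offers. In cells that small, the share of DCD donors or of very old donors will vary by chance. If these factors predict acceptance, the variation adds noise to the treatment contrast, and in the one realised trial it may happen to favour one condition. A covariate fixed before the acceptance decision can remove part of that noise without touching the path from biopsy access to acceptance. At stake are a few points of power at most, and a result that is easier to defend if the donor mix turns out uneven between conditions.

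**Working it through.** **1. Inputs from the article**

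- Rates: "would represent an increase from 28% to 39% acceptance", so the difference is δ = 0.11.
- "Assuming an average cluster-period size of 18", so m = 18.
- WP-ICC ρ = 0.03 and CAC π = 0.92 (*First primary outcome*).
- 20 clusters, 5 steps, 4 clusters crossing at each step (Figure 3 legend), hence T = 6 periods.
- "The primary outcomes will be compared using two-sided tests and at a 2.5% significance level" (*Analysis plan*), so z = 2.2414.

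**2. Reproducing the stated power**

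Binary variance, averaged over the two conditions: s² = (0.28 × 0.72 + 0.39 × 0.61)/2 = 0.21975.

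Variance components of a cell mean:

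- a = s²[ρ(1 − π) + (1 − ρ)/m] = 0.21975 × (0.0024 + 0.05389) = 0.01237
- b = s²ρπ = 0.21975 × 0.0276 = 0.006065

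Design sums for the complete wedge, with K = 20:

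- U = 60 (intervention cells)
- W = 880 (squared period totals, summed)
- V = 220 (squared cluster totals, summed)

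Var = K·a·(a + T·b) / [(KU − W)·a + (U² + KTU − TW − KV)·b]

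Here KU − W = 320 and U² + KTU − TW − KV = 1120. So Var = 20 × 0.01237 × (0.01237 + 0.03639) / (3.958 + 6.793) = 0.001122, and SE = 0.0335.

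Power = Φ(0.11/0.0335 − 2.2414) = Φ(1.043) = 85.1%. The article states 85%, so its figure stands with no covariate in the model. With the 22 randomised clusters the same method gives 88.6%.

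**3. Effect of adding donor age and type**

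The article gives no R² for these factors. As an assumption, R² runs from 1% to 15% and reduces only the offer-level part of the variance: a = s²[ρ(1 − π) + (1 − ρ)(1 − R²)/m], with b unchanged (20 clusters, m = 18).

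| Assumed R² | SE | SE ratio | Power | Gain (points) |
|---|---|---|---|---|
| 0 | 0.0335 | 1.000 | 85.1% | – |
| 1% | 0.0334 | 0.996 | 85.5% | 0.3 |
| 2% | 0.0332 | 0.992 | 85.8% | 0.6 |
| 5% | 0.0328 | 0.979 | 86.8% | 1.6 |
| 10% | 0.0320 | 0.956 | 88.3% | 3.2 |
| 15% | 0.0313 | 0.933 | 89.9% | 4.8 |

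These SEs are on the linear, risk-difference scale. They serve to gauge test power and do not describe the log odds ratio.

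**4. What R² might be**

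If DBD and DCD offers were evenly split, an assumed acceptance gap of d gives R² ≈ d² × 0.25/s². For d = 0.10 this is 0.0025/0.21975 = 1.1%; for d = 0.20 it is 0.01/0.21975 = 4.6%. Age would add something, though its range is cut off at 60. Reaching 10% to 15% from donor type alone would need a gap of about 30 to 36 points (√(0.10 × 0.21975/0.25) = 0.30; √(0.15 × 0.21975/0.25) = 0.36). The lower rows of the table should therefore not be taken as the expected case.

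**5. Does drift in donor mix bias the unadjusted estimate?**

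This was simulated with 1,000 runs per scenario, linear-scale generalised least squares and random crossover order. The true effect was 0.11 and the donor-type effect −10 or −20 points. The donor-type share had no drift, a common drift of 20 points, a centre-specific drift with SD 20 points, or both.

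| | Mean estimate | Empirical SD |
|---|---|---|
| Unadjusted | 0.109 to 0.111 | 0.033 to 0.034 |
| Adjusted | 0.109 to 0.111 | 0.032 to 0.034 |

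The Monte Carlo error of each mean is about 0.001 (0.033/√1000), so neither analysis shows bias. The gain in precision is small, in line with R² of about 1% to 5%.

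**The case against.** The strongest reply is that nothing here is an error. The stated model is a standard stepped-wedge model. It has the same terms as the model from which the WP-ICC and CAC were estimated, so past drift in donor mix is already within those values. The planned power is met, donor type and age over 70 are examined as subgroups, and an adjusted analysis may sit in the analysis plan that is not shown. All of this stands and keeps the point modest. It does not remove the point, because the article itself fixes the model for the hypothesis test.

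A reader might infer that the model corrects for period alone and leaves the effect open to case-mix drift. The documents do not support that. Cluster and cluster-by-period effects are in the model, drift common to all centres goes into the period effects, and centre-specific drift is chance noise because crossover order is randomised. Nor do they support a large gain: no figure in the article justifies assuming a high R².

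Two technical objections also stand and shape the remedy. In a logistic model, prognostic covariates usually raise the standard error of the log odds ratio and make the odds ratio conditional, so the benefit lies in test power. And an identity-link binomial model with two random effects and a continuous covariate may not converge.

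Finally, the article does not settle whether biopsy access could change which offers a centre receives. The age and type of the donor behind any given offer are nonetheless fixed before the decision on it.

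**Conclusion.** The point holds as a missed, inexpensive improvement to a stated model. Adjusting for donor age and type would raise power from 85.1% to between about 85.5% and 90% if R² lies between 1% and 15%, and by only 0.3 to 1.6 points if it lies between 1% and 5%. It would also guard against chance donor-mix imbalance in the realised trial. These figures rest on 20 clusters, a cluster-period size of 18, the article's WP-ICC and CAC, a linear approximation, and an R² range that is assumed. Priority is low to moderate.

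**What to change.** Before outcome data are seen:

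- Pre-specify donor age (continuous) and donor type (DBD/DCD) as fixed effects in the first primary logistic model, alongside period, cluster and cluster by period.
- Keep the model now stated as a sensitivity analysis.
- Obtain the adjusted risk difference and its interval by standardising from the adjusted logistic model, and do not add covariates to the identity-link model.
- Do not add donor factors to the primary eGFR model. Its population is selected by the acceptance decision that the service is meant to change, so the donor mix among transplanted kidneys may be part of the service's effect.

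The cost is a line or two of analysis wording and no new data collection. The odds ratio must then be described as conditional on donor age and type.
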